#### Secondary analysis

Secondary outcome measures will include the safety and tolerability of the study drug. These end points will be assessed among all subjects who have taken at least one dose of trial medication (including subjects who vomit within 1 hour of study drug administration).

The number of safety events* as measured by side effects and adverse events as well as tolerability reported by participants will be evaluated. The safety events will be tabulated by treatment allocation, event grade, severity and relatedness to study treatment [35]. The tolerability will be defined as the ability of participants to ingest all or at least 7-days or 14 doses of cefixime without experiencing treatment-related side effects or adverse events that cause the patient to discontinue the medication or that prevent the participant’s ability to complete the full course of treatment. The number of participants discontinuing therapy due to intolerance of cefixime will be reported.

**The types of safety events as collected on the side effects and adverse reporting questionnaires will be based on the period of medication administration (10 days) and at 14 and 30 days following the first dose of treatment.*

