### Schedule and content of study follow up visits and telephone encounters

#### Study Visit 1 at day zero: Non-pregnant, HIV negative women with positive treponemal test and RPR titer ≥1:16 and meeting inclusion criteria will be offered enrolment

Informed consent will be completed by a study nurse prior to RPR testing, and baseline clinical information including symptom review, medical and sexual history, physical exam will be collected. Patients not consenting to participate in the study will receive treatment per national treatment guidelines for syphilis.

Subject data will be collected on study specific case report forms. Baseline treponemal result and RPR titer, signs and/or symptoms of syphilis and other STIs, will also be collected. Data will be entered into a central database using patient identification numbers only. Venipuncture will be performed, and blood will be collected for RPR quantitative titers Table 3.

**Table 3 Tab3:** Schedule of venipuncture specimen collection visits

Visit number	Scheduled visit	Allowed specimen collection interval outside of scheduled visit date
1	Screening	RPR test, HIV (eligibility checking)
2	Enrolment	Not applicable
3	3 months	10 days before or 45 days after
4	6 months	44 days before or 45 days after
5	9 months	44 days before or 45 days after

Once specimens have been collected and RPR results return at values equal to or greater than 1:16, subjects will be randomly assigned to one of two groups:
Group A: standard of care or penicillin groupGroup B: experimental group or cefixime group

Participants of Group A will receive treatment for syphilis with BPG according to national STI treatment guidelines. Participants in group A will be instructed to remain in the clinic for observation for 30 minutes after receiving this penicillin injection. According to national syphilis treatment guidelines, patients receiving penicillin may be asked to return for additional injections. These study participants will be asked to visit the clinic 3, 6 and 9 months after the day they received BPG for evaluation and RPR testing. BPG will be provided by the Brazil Ministry of Health.

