Participants of Group B will receive their first dose of 400 mg cefixime at the study clinic under direct observation. Patients receiving cefixime will be instructed to remain in the clinic for observation for 30 minutes after receiving the medication. Participants will be given the cefixime pills and instructed on how and when to take their medication at home which they must continue for 10 days. Daily phone calls and text messages will be made to the patients by a study nurse to ascertain adherence to study medication and record side effects. Patients will be asked to bring back any unused study medication to their next visit two weeks following enrolment. Study participants receiving cefixime will also be asked to return to the clinic for scheduled visits 3, 6 and 9 months after the day of the last dose of cefixime for evaluation and RPR testing.

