#### Study Visit 2 at two weeks following enrolment (allowable two days before or five days after scheduled visit):

Participants receiving cefixime will return to the clinic two weeks after enrollment for assessment of treatment compliance, evaluation resolution of symptoms if present at enrollment, and to ascertain any toxicities. Subjects will be asked to return for a scheduled clinical and laboratory assessment (Study Visit 3) at three months following enrollment.

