### Phone call at 30 days following enrolment

A phone call to study participants randomized to cefixime will be conducted to perform a final evaluation of safety (side effects and adverse events) following the completion of the course of study drug.

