#### Study Visit 4 at six months following enrolment (allowable 44 days before or 45 days after scheduled visit):

Subjects that received either cefixime or BPG will be asked questions regarding their current symptoms, interval sexual history, concomitant antibiotic use and possible adverse reactions if they received cefixime. Subjects will have a venipuncture blood specimen collected for syphilis testing (RPR) increase in RPR titer at 3 or 6 months post treatment. Those subjects who experience a fourfold (two titer) increase in RPR titer at three or six months post treatment will be considered a treatment failure and will receive BPG 2.4 million units IM once per week three weeks. Data for these patients through Study Visit 4 will be included in analyses, and for analysis purposes, these patients will be considered to be treatment failures. All participants will undergo pregnancy testing. Those that are found positive on pregnancy testing will be treated for syphilis according to national guidelines and removed from the study. A voluntary repeat HIV test will be performed at 6 months. Patients that test positive for HIV at 6 months will be referred for HIV care. No additional treatment for syphilis will be provided based on HIV-positive status other than according to the study protocol. Response to treatment of these patients will be included in the analysis. Subjects that received either cefixime or BPG will be asked to return at 9 months from the time of treatment.

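### The by-arm safety table covers a window in which only the cefixime arm is scheduled to be asked about side effects, so its two columns are not comparable

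*Protocol article*

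**What the plan says.** All references are to the protocol article.

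*Secondary analysis* commits to a table with both arms in it: "The safety events will be tabulated by treatment allocation, event grade, severity and relatedness to study treatment". Its footnote fixes when events count. The types of safety event collected on the questionnaires "will be based on the period of medication administration (10 days) and at 14 and 30 days following the first dose of treatment".

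The contacts in that window are these:

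- **Daily calls.** In the Group B (cefixime) paragraph under *Study Visit 1*: "Daily phone calls and text messages will be made to the patients by a study nurse to ascertain adherence to study medication and record side". The item cut off at the end of this quote is side effects.
- **Two-week visit.** Under *Study Visit 2*: "Participants receiving cefixime will return to the clinic two weeks after enrollment for assessment of treatment compliance". The same sentence adds toxicities to the purpose of the visit.
- **30-day call.** "A phone call to study participants randomized to cefixime will be conducted to perform a final evaluation of safety".

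For BPG, *Study Visit 1* gives observation on the day of injection: "Participants in group A will be instructed to remain in the clinic for observation for 30 minutes after receiving this penicillin injection". It allows for returns for further injections and then sets the follow-up: "These study participants will be asked to visit the clinic 3, 6 and 9 months after the day they received BPG for evaluation and RPR". This quote breaks off at the serological test. *Study Visit 3* (month 3) and *Study Visit 5* (month 9) ask both arms about possible adverse reactions. *Study Visit 4* (month 6) asks about "possible adverse reactions if they received cefixime".

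**The concern.** A table by allocation invites the reader to set one column against the other. That is fair only if events were sought in the same way in both arms. Here one arm is questioned repeatedly throughout the window and the other has no stated questioning in it. The trial is open label, so blinding does not even out what is reported spontaneously.

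Mild and transient events, such as the gastrointestinal complaints that *Potential risks* lists for cefixime, depend most on being asked about. If they go unrecorded on BPG, cefixime looks relatively less well tolerated than it is. Safety is the only secondary objective, and the trial is meant to inform a later one in pregnant women, so this table is likely to be read closely. An analysis plan cannot repair it afterwards, because events that were never elicited cannot be tabulated.

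**Working it through.** The plan gives no figure for this point. Its only calculated number is the efficacy sample size, which does not enter here. The check is therefore a comparison of schedules, followed by an illustration.

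**1. Contacts stated to ask about side effects, by arm**

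| Time | Cefixime | BPG |
|---|---|---|
| Day 0 | 30 minutes of observation | 30 minutes of observation |
| Treatment days | Daily calls, about 10 | None stated |
| Two weeks | 1 visit | None stated |
| Day 30 | 1 call | None stated |
| Month 3 | Asked | Asked |
| Month 6 | Asked | Not asked |
| Month 9 | Asked | Asked |

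After day 0 and up to day 30, cefixime has 10 + 1 + 1 = 12 such contacts, taking one call per treatment day. BPG has 0. Return visits for injections may occur, but no adverse-event questions are described for them.

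**2. Does the first BPG question fall inside the window?**

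The month-3 visit may take place up to 10 days early. Taking three months as about 90 days, the earliest date is 90 − 10 = day 80, which is 80 − 30 = 50 days after the window closes.

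**3. Illustration of size**

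Inputs: 140 cefixime and 70 BPG women (*Randomization*). A true 30-day risk of 30% is assumed equal in both arms. The figure is borrowed from the gastrointestinal event rate for cefixime in *Potential risks*; the documents give no BPG rate. Capture is assumed complete on cefixime. The share *s* captured on BPG is unknown, so it is varied.

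Expected cefixime count = 140 × 0.30 = 42 (30%). Expected BPG count = 70 × 0.30 × *s*. Apparent risk ratio = 0.30 / (0.30 × *s*) = 1/*s*.

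| *s* | BPG count of 70 | BPG % | Spurious difference | Apparent risk ratio |
|---|---|---|---|---|
| 100% | 21 | 30% | 0 points | 1.0 |
| 75% | 15.75 | 22.5% | 7.5 points | 1.33 |
| 50% | 10.5 | 15% | 15 points | 2.0 |
| 25% | 5.25 | 7.5% | 22.5 points | 4.0 |

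The ratio does not depend on the assumed risk, but the difference does. With 16% instead (the diarrhoea figure in the same section), the difference is 0.16 × (1 − *s*): 4, 8 and 12 points at 75%, 50% and 25% capture.

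**The case against.** **No comparison is planned.** *Methods/design* calls the trial non-comparative, the secondary outcome is the safety of cefixime alone, and no safety test, difference or ratio is specified. This stands, and it limits the point to a descriptive table. It does not remove the point. The sentence ruling out direct comparison, under *Participant recruitment*, concerns the performance of BPG and gives lack of power as the reason. The table by allocation remains, and unequal elicitation is not a matter of power.

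**The schedule may cover both arms.** The inclusion criteria require every woman to accept daily calls and a 14-day visit, and *Intent-to-treat (ITT) population* speaks of daily calls to participants generally. But the inclusion criteria record willingness before allocation, and the calls in the ITT section serve adherence to medication and reminders of the evening dose, which fits the oral course. The sections that describe the two-week visit and the 30-day call name cefixime recipients. If both arms were intended, those sections need correcting. The month-6 restriction may well be a drafting slip, since months 3 and 9 carry no such limit.

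**BPG women are not without contact.** They are observed on day 0, may return for injections, and may recall early events at month 3 or 9. This is fair, and it is why a reader should not infer that the BPG column will be near zero. The documents give no capture rate.

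**Two further inferences are not supported.** One is that any excess on cefixime would be artefactual: an oral cephalosporin may truly cause more gastrointestinal events than an injection, and the documents cannot separate the two. The other is that the trial could not inform the later study in pregnancy: the cefixime rate is collected intensively, and no decision is tied to a safety contrast with BPG.

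**Conclusion.** The point holds as a matter of differential ascertainment in a descriptive table. Followed as written, the protocol prints cefixime and BPG safety columns for a window in which the scheduled side-effect questioning is about 12 contacts against 0. The probable direction is under-reporting on BPG.

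The size cannot be derived from the documents. The apparent risk ratios of 1.33 to 4.0 rest on an assumed equal true risk, full capture on cefixime and BPG capture of 75% down to 25%. With equal capture there is no spurious difference.

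The percentage of cefixime women with adverse events is unaffected, and so is the efficacy analysis. The change is worth making, but the trial's main conclusions do not depend on it.

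**What to change.** **Reporting, at the cost of wording only.**

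- Present cefixime safety as a single-arm result.
- Limit any table by arm to events elicited in the same way in both arms.
- Show cefixime events from the daily calls, the two-week visit and the 30-day call separately, and mark early BPG events as not actively solicited.
- State whether BPG counts as trial medication in the definition of the safety set, which *Secondary analysis* leaves unclear.

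**Consistency.** Reconcile the month-6 wording in *Study Visit 4* with months 3 and 9, so that both arms are asked about adverse reactions.

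**Optional, for women still to be enrolled.** Use the same day-14 and day-30 questionnaire by telephone in the BPG arm. The cost is at most 70 × 2 = 140 short calls, plus an amendment through the ethics committees; *Ethics approval and consent for participation statement* lists seven approving bodies. The inclusion criteria already ask every woman to accept daily calls and a 14-day visit. Enrolment had begun by the time the eligibility criteria were amended, and *Data Availability* describes collection as ongoing. The calls cannot recover early events in women already past day 30, so the reporting change is needed in any case.

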### Data collection and management

Study data will be collected on paper case report forms (CRFs) approved by the internal form review committee and key-entered at the respective collaborating research institute. The WHO study team in Geneva has developed a customized web-based electronic data capture (EDC) system using Open Clinica Enterprise platform for entering, cleaning, and tracking study data. The web-based data capture system will be designed to ensure that only authorized staff can enter, change, or view data. The local study data management teams will be trained in data collection, online data entry, and data management using the EDC system. The EDC system will perform edit checks during the data entry process to notify immediately of potential errors and inconsistencies. Using this system, the data will be available in the study database and accessible to the WHO study team for review of information as soon as the data are entered at the local site. Double data entry will be used. The local study team will keep an updated log of screened and enrolled study participants. WHO team will liaise with the local study team to coordinate and track CRF completion and data queries. The database will be locked after all queries have been resolved and analyzed at WHO.

### Data safety and study monitoring

The study will be followed by a Data Safety Monitoring Board (DSMB). The DSMB will be composed of 5 members: (1) Physician/Clinical researcher; (2) Biostatistician; (3) Ethicist; (4) Epidemiologist; and (5) Infectious diseases, microbiologist. A data safety and monitoring plan (DSMP) includes the terms of reference for the DSMB, interim analysis tables and study stopping rules. This DSMP is available upon request ([contact]; [contact]).

External monitoring of clinic recruitment sites will be performed by Fiocruz, Brazil at study initiation, during three follow up visits and at study completion.

The data monitoring committee consists of 2 WHO biostatisticians, one clinical trials data collection and monitoring expert, two WHO medical officers responsible for the trial and one non-study related WHO staff.

### Ethical concerns

#### Potential risks

Potential risks to study participants include the possibility that the alternative treatment may not prove to be effective. For this reason, we will closely follow the subjects for adherence to study medication including daily phone or in-person contact to establish adherence to study drug. RPR titers will be collected 12 weeks after completion of treatment (with no more than 5-day result turnaround time). If the participant experiences an RPR titer increase of 4- fold or more from the entry RPR at 3 or 6 months, we will consider this a treatment failure and the participant and be given 2.4 million units of BPG immediately and according to national guidelines.Risks to privacy: Participants’ attendance at study visits may be accidentally noticed by others.Psychological risks: Receiving a positive syphilis diagnosis could be upsetting to a participant. However, syphilis diagnosis occurs as part of standard clinical care and outside of the study.*Risks associated with blood draw*: Participants may experience discomfort, bruising, or even fainting in connection with the blood draw that will be performed during the visits. There is also a slight risk of infection.Cefixime is contraindicated in patients with known allergy to cefixime or other cephalosporins. Some participants may not be aware of their allergy status. However, anaphylactic or anaphylactoid reactions (including shock and fatalities) have rarely been reported with the use of cefixime, thus this risk is considered to be very low.Some adverse reactions were documented in other cefixime clinical trials. In United States (U.S.) trials of the tablet formulation of cefixime, the most commonly seen adverse reactions were gastrointestinal events. These events were reported among 30% of adult patients that received either the twice daily or the once daily regimen. Discontinuation of cefixime during the U.S. clinical trials occurred among 5% of study participants because of drug-related adverse reactions. Other individual adverse reactions reported from U.S. clinical trials included diarrhea (16%), nausea (7%), loose or frequent stools (6%), flatulence (4%), abdominal pain (3%), and dyspepsia (3%). Observed and reported adverse reactions for cephalosporins including but not limited to cefixime have included allergic reactions, superinfection, renal dysfunction, toxic nephropathy, hepatic dysfunction including cholestasis, aplastic anemia, hemolytic anemia, hemorrhage, and colitis.In this study, participants will be observed for 30 minutes in the clinic following the first dose of cefixime. In the event of an adverse event or an allergic reaction possibly related to cefixime, participants will be evaluated by a study nurse and by a clinic-based study physician. Participants will be referred to emergency services at the discretion of the clinic-based study physician. Cefixime will be discontinued in the event of an allergic reaction.The efficacy of cefixime to prevent mother-to-child transmission of syphilis is unknown. Study participants will be counseled regarding the risk of untreated syphilis in pregnancy. Each participant will be offered oral contraceptive tablets as well as condoms to prevent pregnancy for the duration of the study. Condoms will be provided to each participant and use will be encouraged at each visit to reduce the risk of re-infection with syphilis and infection with other STIs.

### Risk management procedures and adequacy of resources

Blood draw: We will ensure that the staff person performing the blood draw is a trained and certified phlebotomist. All standard precautions against infection will be taken.Before therapy with cefixime is instituted, careful inquiry will be made to determine whether the patient has had previous hypersensitivity reactions to cephalosporins, penicillins, or other drugs.Patients found to be pregnant at follow-up visits will be removed from the study and given an injection of 2.4 million units of BPG.Sexual partners of enrolled patients will be solicited and offered treatment as per the national guidelines.Patients will be offered contraception for the duration of the study to prevent pregnancy that could be affected by untreated or under-treated syphilis. Oral or injectable contraceptive will be offered to patients according the choices available on clinic-site formularies.

If a study participant suffers an injury or illness related to this research, they will be instructed to contact the Principal Investigator immediately. If it is determined by a doctor, not associated with this study, that the injury or illness is definitely related to the study drug “cefixime” or a study related procedure, medical care will be provided or arranged. Costs associated with study-related injuries (physical, psychological, social harm, or loss of wages) will be covered by the study at no cost to the participant. In no way does signing the consent form waive their legal rights nor does it relieve the investigators or involved institutions from their legal and professional responsibilities. This information is included in the consent form.

### Privacy and confidentiality considerations including data access and management

#### Consenting, screening, and study visit

The informed consent procedure is designed to maximize the potential participant’s comprehension of study procedures and to ensure that participation is voluntary. Before a participant is enrolled, a study nurse will explain the study’s purpose, the procedures to be followed, and the risks and benefits of participation. A copy of the consent form, which includes a description of the study, will be provided to all participants. The study nurse will assess whether the potential participant has understood the study and consent form by asking key questions related to participation. If a potential participant decides at any point during the informed consent process that they do not wish to participate, her decision will be honored regardless of how well she comprehends the study information.

The consent process will be conducted in a private exam room. The level of linguistic difficulty (vocabulary, sentence length and complexity, etc.) will be kept at a basic (approximately fourth-grade) level to ensure maximum comprehension. Once written informed consent is obtained, the first study procedure (specimen collection) will take place immediately.

